#### Joint flexibility and triceps surae mechanics

Lower limb joint flexibility will be assessed using three tests: the modified Thomas test, the passive knee extension test and a passive ankle dorsiflexion test. In the modified Thomas test, three measurements are performed at the hip joint and 2 at the knee joint [72]. The first hip measure has the goniometer fulcrum at the greater trochanter of femur, reference lines using lateral femoral condyle and a line perpendicular to the bench. The second hip measurement is like the first, however the researcher will apply a hip extension torque at the distal thigh and will record the angle at which the subject reports initial stretch pain sensation. The third hip measure has the goniometer fulcrum at the anterior superior iliac spine, references lines using the superior aspect of the patella and a line parallel to the bench. The first knee measure has the goniometer fulcrum at the lateral femoral condyle, reference lines using lateral malleolus and greater trochanter of femur. A limitation of the knee angle to access two-joint hip flexors flexibility is that it is directly affected by the hip angle 1 (one-joint hip flexors). Thus, the second knee angle is measured with the participant in the same position, except that the thigh of the tested leg is supported on the bench (instead of hanging outside of it), thus hip angle will be 0°. It should be noted that only hip measurement 2 is a flexibility test, because attaining maximum ROM requires unlimited torque and the subject acknowledging stretch sensation pain. On the other four measurements, the joint angle attained is a result of the interaction between gravity and the joint’s passive resistance to stretch. Thus, a stiffer joint will not yield much to the gravity force, and the reduced ROM cannot be mistakenly interpreted as poor flexibility. Although not true flexibility tests, these measurements provide important information about how different muscles affects the lower limb joints.

The passive knee extension test is performed in the same position as the hamstring stretch with the participant lying supine with hip and knees at 90°. The non-tested thigh is strapped to the bench to avoid pelvic retroversion during the test. The examiner slowly applies torque at the posterior aspect of the shank causing knee extension, while another examiner maintains the hip position. The test stops when the participant acknowledges an initial stretch pain sensation. A similar knee angle measurement used in the modified Thomas test is performed. A manual goniometer is utilized to perform the both tests.

The passive dorsiflexion test will be performed using the same motor-driven dynamometer utilized for the ankle strength tests. The participant will seat with the hip joint flexed at 60°, ankle at 35.5° of plantarflexion and knee on two possible positions: 90° or 0°. The examiner will slowly (< 5°/s) move the device causing ankle dorsiflexion until the participant acknowledges an initial stretch pain sensation. Another criterion to stop the test is a heel raise higher than 5 mm. Since the motor-driven dynamometer will be also utilized subsequently to perform very fast dorsiflexions for the TSRT test, for safety reasons the maximum attained dorsiflexion angle is 21°. Thus, it is possible that maximal ROM is not measurable for some participants in the extended knee position. Three to five trials in each knee position will be performed and the maximum ROM for each position and leg will be reported. From the passive dorsiflexion torque-angle curve, in the region encompassing 20–80% of the participant’s peak torque [51], average joint stiffness (i.e. first derivative), energy (i.e. integral) and hysteresis (difference between loading and unloading integral) will be calculated. Additionally, these variables will be calculated utilizing absolute joint angles. Trials with triceps surae EMG RMS higher than 3 SD of resting levels will be discarded (EMG setup 1). Table 4 presents the criteria for each joint flexibility measurement based on TD normative data [97–103].

**Table 4 Tab4:** Joint flexibility tests and references from typically developing controls attained in other studies

Reference Values and Diagnostic	
**Modified Thomas test**	
Hip measurement 1: Hip angle > 0° = short and/or stiff one-joint hip flexors (i.e. iliopsoas, hip adductors).	
Hip measurement 2 (examiner applies hip extension torque): Hip angle > 0° = short one-joint hip flexors.	
Hip measurement 3: Reference value = 0° (i.e. ASIS and patella aligned on the sagittal plane). Positive values = short and/or stiff hip abductors.	
Knee measurement 1: Knee angle < 67° = short and/or stiff two-joint hip flexors (i.e. rectus femoris, tensor fascia latae, sartorius).	
Knee measurement 2 (supported hip): Knee angle < 67° = short and/or stiff two-joint hip flexors.	
Note: Tightness of the anterior capsule and ligaments may also influence the test.	
References: [72, 97–99]	
**Passive knee extension test**	
Knee angle > 40° (with the hip at 90°) = short hamstring muscles.	
References: [100, 101]	
**Passive ankle dorsiflexion test**	
Ankle angle < 18° with knee at 0° and 90° = short Soleus muscle.	
Ankle angle < 18° with knee at 0° and ankle angle > 18° with knee at 90° = short Gastrocnemius muscle.	
Ankle angle **>** 18° in with knee in 0° and 90° = good triceps surae flexibility.	
References: [102, 103].	

*ASIS* anterior superior iliac spine. Hip measurements 1–2: 0° = anatomical position, positive values = hip flexion. Knee measurements: 0° = knee in full extension. Ankle measurements: 0° = sole of the foot at right angles to the tibial axis, positive values = dorsiflexion

Neuromechanical responses during the TSRT protocol (i.e. 40 stretches at 4 velocities) will also be analyzed. The higher stretch velocities in this protocol will result in reflex muscle activation, thus involving both passive and active elements. First, mechanical artifacts at the beginning and end of each stretch will be removed, then peak and mean torque, joint stiffness and energy will be calculated for each stretch. Additionally, maximum EMG RMS (EMG setup 1) will be calculated with a 50 ms moving window for each stretch. Comparisons between velocities and between the first and last group of 8 stretches will be performed to gain insight into the differences in neuromechanical responses to dynamic repetitive stretching.

#### Physical activity

PA will be assessed using questionnaires and device-based measurements. The questionnaire from Jackson et al. [104] with a scale from 0 to 7 describing the overall PA level is complemented by questions about the amount of moderate-to-vigorous PA during a week. PA will also be measured with a tri-axial waist-worn accelerometer (X6-1a, Gulf Coast Data Concepts Inc., Waveland, MS, USA) with a dynamic range of ±6 g and a sampling frequency of 40 Hz. The accelerometer will be utilized during seven typical days at three time points: control, intervention and maintenance periods. A minimum of 3 days with 8 h of measurement will be accepted for analysis as it has been shown to provide adequate reliability for children and adolescents with CP GMFCS I [105]. Raw acceleration data will be transformed to Actigraph counts [106], in order to utilize validated GMFCS specific thresholds for different intensity zones for children with CP [107].

Specialized shorts with textile electrodes (Myontec Ltd., Kuopio, Finland, 108) will be utilized to record EMG bilaterally from quadriceps and hamstring muscles during an entire typical day. A small recording electronic module is able to collect muscle activity data for 8–12 h and can be analyzed offline afterwards. EMG signals will be acquired with a sampling frequency of 1 KHz and band-pass filtered (50–200 Hz, − 3 dB). The raw signals will be full wave rectified and averaged over 100 ms non-overlapping windows and stored into a portable module. Daily muscle inactivity, light, moderate and vigorous activity time of the participant will be extracted [108, 109]. Muscle inactivity will be defined as < 90% of the standing EMG activity for each muscle group. Moderate activity threshold is the preferred walking EMG activity, and vigorous activity is twice the amplitude of walking [110]. The participants will receive a diary to record times when the accelerometer and EMG pants are worn, facilitating the removal of non-wear time in the analysis.

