### Study purpose

The present study has three aims: 1) to investigate the effects of the EXECP intervention on the following variables: gait performance (primary outcome), physical activity level, lower limb muscle strength and joint flexibility, gross motor function, cardiometabolic risk factors, neuromuscular parameters for triceps surae muscle, cortical processing of proprioceptive stimuli evoked by passive ankle dorsiflexions, tibialis anterior (TA) cortico-muscular and intramuscular coherence; 2) to evaluate the retention of the adaptations induced by the intervention after three months; 3) to compare CP and typically developing (TD) individuals in all studied variables using group and matched (age/sex) individual data. The EXECP intervention is composed of a three-month individually tailored exercise intervention containing strength training targeting lower limb and trunk muscles, combined with stretching of diagnosed short muscles and gait training. The primary hypothesis is that the EXECP intervention will enhance gait performance by: a) increasing walking distance in the 6 min walking test; b) increasing ankle dorsiflexion during the swing and stance phase of gait; c) increasing maximal walking velocity, joint net moments and ranges of motion in the lower limb joints. The secondary hypothesis are that the EXECP intervention will: d) increase habitual PA; e) increase maximal isometric and concentric torque and rate of force development for the trained muscles; f) not affect cardiometabolic risk factors such as arterial stiffness, insulin resistance, blood lipids and body fat content; g) increase gross motor function measure (GMFM; [19]) score; h) increase lower limb joint flexibility of the trained muscle groups; i) decrease ankle plantarflexors average joint stiffness and increase joint energy (i.e. area under the torque-angle curve) during slow passive stretching; j) decrease antagonist muscle electromyography (EMG) during maximal voluntary isometric and concentric plantarflexion and dorsiflexion; k) not change spinal mechanisms related to hyperreflexia in the Sol muscle (i.e. Hoffmann-reflex (H-reflex), post-activation depression (PAD) ratio, tonic stretch reflex threshold (TSRT)); l) increase amplitude of cortical responses to proprioceptive stimulation, recorded with magnetoencephalography (MEG) in the primary somatosensory cortex; m) increase cortico-muscular coherence between cortical MEG and TA EMG signals; n) increase intramuscular coherence within TA muscle during a submaximal isometric dorsiflexion and during the swing phase of the gait cycle. No changes in any of the studied variables are expected during the 3-months control period, except if the participant is going through the growth spurt. After the 3-month maintenance period, the values of the studied variables are expected to be in between the control and post intervention values (project aim B). All study variables are hypothesized to show differences between the TD and CP groups (project aim C). It is expected that the comprehensive assessment battery of neuromuscular, brain, cardiometabolic and functional parameters will add valuable information about how people with CP adapt to exercise.

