### Study procedures

The EXECP intervention will mainly take place at the NMRC, although it can be performed in other gyms having all required training equipment. It consists of two to three training sessions per week for 12 weeks. The number of weekly sessions will depend on the level of PA of each participant: those engaged in regular weekly PA may choose to perform 2 or 3 sessions, while sedentary participants will train 3 times per week. Training sessions are 90 min in duration and are separated by at least 48 h. Each training session starts with an inclined treadmill walking (5–10 min), followed by strength (60–75 min) and flexibility training (10–20 min). To ensure optimum training quality all sessions are performed individually and supervised by a strength and conditioning coach or a physiotherapist with full understanding of the training protocol.

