### Gait training

A portable mechanical treadmill with an inclination of 6° or 7.3° (Vida XL, Venlo, Netherlands) will be utilized for training. Participants are instructed to walk at a comfortable speed, avoiding toe walking and trying their best to attain heel strike. A non-motorized treadmill was chosen because belt movement is attained by pushing it with hip extension and ankle plantarflexion, reinforcing a correct pattern of muscle activation. Verbal feedback will be constantly given during the warm-up to improve gait quality, and the participant will be allowed to stop and rest whenever necessary. In addition to 5–10 min of gait training in every session, all participants will receive a treadmill to take home, and are asked to walk a minimum of 10 min per day every day for the duration of the intervention. An exercise diary will be filled by the participants or their guardians to document the weekly walking durations. During the maintenance period, the participants will choose if they want to keep using the treadmill at home and updating their diary or stop and return it.

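### The intervention-period accelerometer week includes EXECP's own prescribed daily walking, so a rise from control to intervention cannot by itself show that habitual physical activity increased

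*Protocol article*

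**What the plan says.** All references are to the protocol article.

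- **Hypothesis.** Under Study purpose, secondary hypothesis d is that EXECP will "increase habitual PA".
- **Measurement.** Under Physical activity: "The accelerometer will be utilized during seven typical days at three time points: control, intervention and maintenance periods". No accelerometer recording at a post-test is listed. On the minimum record: "A minimum of 3 days with 8 h of measurement will be accepted for analysis".
- **Data removal.** Participants keep a diary of when the accelerometer and EMG shorts are worn, its stated purpose being "facilitating the removal of non-wear time in the analysis". No step for separating EXECP activity from other activity is described.
- **Prescribed walking.** Under Gait training, all participants receive a home treadmill and "are asked to walk a minimum of 10 min per day every day for the duration of the intervention". On the record kept: "An exercise diary will be filled by the participants or their guardians to document the weekly walking durations".
- **Supervised sessions.** Under Study procedures there are two or three 90-min sessions a week for 12 weeks. "Each training session starts with an inclined treadmill walking", lasting 5–10 min.
- **Maintenance period.** Supervised training has ended, and "the participants will choose if they want to keep using the treadmill at home and updating their diary or stop and return it".
- **Usual activities.** Study design asks participants to keep these stable. It allows a reduction during the intervention to avoid overload, and important deviations will be reported.

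**The concern.** Habitual activity is what a participant does apart from the programme. The intervention-period recording cannot isolate that, because the programme prescribes walking on every day from which the recording can be drawn. Asking for typical days does not help: while the intervention runs, a typical day is one with prescribed walking.

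At stake is the reading of hypothesis d. If PA is higher in the intervention week than in the control week, participants may have become more active in daily life, or they may simply have done the prescribed walking. The later course need not settle it. Study purpose expects maintenance values to lie between the control and post-intervention values, as partial retention. Prescribed walking that some participants stop and others continue by choice would give the same group pattern with no change in habitual activity.

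The part that cannot be repaired later is data capture. An analysis plan can choose a contrast, but it cannot recover times of home walking that were never written down.

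**Working it through.** The article gives no baseline, SD, effect size or power for PA, so there is no figure to reproduce. The check is the prescribed dose, followed by an illustration of what it could do.

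**Inputs.** Home walking at least 10 min/day on 7 days a week (Gait training). Treadmill walking in sessions 5–10 min, 2–3 sessions a week (Study procedures). Minimum accepted record 3 days of 8 h (Physical activity).

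**Step 1: dose in a full week, at full adherence.**
- Home walking: 7 × 10 = 70 min/week, i.e. 10 min/day.
- In-session treadmill walking: 2 × 5 = 10 to 3 × 10 = 30 min/week.
- Together, if the device is also worn in sessions (not stated): 80 to 100 min/week, i.e. 80/7 = 11.4 to 100/7 = 14.3 min/day.

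**Step 2: dose in the smallest accepted record.**
- Wear time: 3 × 8 h = 24 h = 1,440 min.
- Home walking: 3 × 10 = 30 min, and 30/1,440 = 2.1% of wear time.
- Adding in-session walking, with none to all three accepted days being session days: 30/3 = 10 to (30 + 3 × 10)/3 = 20 min/day.

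The planned analysis uses intensity zones derived from counts, so these minutes show only the order of size.

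**Step 3: illustration.** Assumptions: habitual walking H does not change; only home walking is counted; all of it is worn; minutes are interchangeable. Let c be the cut in usual activity during the intervention (min/day) and f the share of participants still walking 10 min/day in maintenance.

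| Period | Recorded | Values | Difference from control (min/day) |
|---|---|---|---|
| Control | H | – | 0 |
| Intervention | H + 10 − c | c = 0, 5, 10, 15 | +10, +5, 0, −5 |
| Maintenance | H + 10f | f = 0, 0.25, 0.5, 1 | 0, +2.5, +5, +10 |

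Two things follow. The intervention week can show a rise, no change or a fall while H is constant. With c = 0 and 0 < f < 1, maintenance lies between control and intervention, which is the pattern expected of a real effect partly retained. Among participants who stop (f = 0), maintenance equals control, so a comparison of those two weeks would correctly show no change.

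**Step 4: can the walking be removed afterwards?** The wear diary gives device times. The exercise diary gives weekly durations. Neither, as described, shows which accepted days or hours held the home walking. Only an approximate correction is possible.

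**The case against.** The best defence is that this is a condensed article, and that the choice of contrast and the handling of exercise time in accelerometer records belong in an analysis plan that is not shown. The article does not say that the intervention week is the test of hypothesis d. Its mixed model is described over pre-tests and post-tests, which do not map onto the three PA periods. The maintenance week is already collected and continuing treadmill users keep their diary, so the cleaner comparison is available. PA is also assessed by questionnaire and EMG shorts.

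Much of this stands. The contrast is unstated, not wrongly stated. What remains is what the article fixes: when the device is worn, what is prescribed on those days, and what the diaries record. The questionnaire is not said to exclude EXECP activity, so it is no clear remedy.

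Several stronger readings are tempting and are not supported:

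- **That PA will be overstated.** Usual activity may be reduced during the intervention, and Step 3 shows that the net change can then be zero or negative.
- **That the distortion is large.** A percentage rise needs a baseline that the article does not give. Counting whole 90-min sessions would also mislead, since they are mostly strength work, much of it seated or supine, with stretching and rests.
- **That adjusting for PA level would remove part of the treatment effect.** Statistical analyses makes adjustment conditional on a strong linear relationship and names no period. Harm would require the intervention-period value to be chosen, a detail commonly left to the analysis plan.
- **That the primary outcome is affected.** Nothing here shows any bias in the six-minute walk.

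**Conclusion.** The point holds as a limit on interpretation and a gap in data capture. The intervention-period accelerometer week contains the treatment, and the diaries as described cannot separate it out. A rise from control to intervention is therefore not, by itself, evidence for hypothesis d.

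The prescribed home walking is at least 70 min a week, or 80–100 min a week with in-session treadmill walking. These figures assume full adherence and a worn device. They are a dose, and neither the direction nor the size of any net distortion is known.

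The maintenance week is cleaner but not fully clean, since home treadmill use may continue by choice. Severity is minor: one device measure for one of eleven secondary hypotheses (d to n), with a nearly free remedy.

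**What to change.** 1. State that hypothesis d is tested on control-week versus maintenance-week accelerometer PA, and report continued home treadmill use in the maintenance period from the exercise diary. This uses data already planned and costs nothing.
2. For remaining participants, add start and stop times of home walking and supervised sessions to the wear diary. Report intervention-week PA with and without that time. This costs a few diary lines and one extra summary.
3. For participants already finished (recruitment began in May 2017), remove supervised-session time where session times are on record, use the weekly walking durations as an approximate correction only, and state the limitation.

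The downside is a more qualified conclusion about PA, with exact exclusion of home walking out of reach for those who have completed the intervention.

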#### Gross motor function

Gross motor function will be assessed in the CP group using the 66-item version of the Gross Motor Function Measure (GMFM-66; [111]). GMFM-66 is a valid, reliable and responsive observational instrument, based on interval scaling to evaluate changes in gross motor function in participants with CP [19]. Dimensions D (standing) and E (walking, running and jumping) will be utilized. The test will be video recorded and scored subsequently by the same evaluator. Absolute and relative (i.e. percentage of maximum) scores for each dimension will be reported.

#### Biological maturity

To control for the confounding effect of maturation on the dependent variables during the study, estimated time from peak height velocity (i.e. maturity offset) will be computed using the sex-specific equation provided by Moore et al. [112]:
$$ \mathrm{Girl}'\mathrm{s}\ \mathrm{maturity}\ \mathrm{offset}=-7.709133+\left(0.0042232\ast \left(\mathrm{age}\ast \mathrm{height}\right)\right);{\mathrm{R}}^2=0.898;\mathrm{SEE}=0.528; $$$$ \mathrm{Boy}'\mathrm{s}\ \mathrm{maturity}\ \mathrm{offset}=-7.999994+\Big(0.0036124\ \mathrm{x}\ \left(\mathrm{age}\ \mathrm{x}\ \mathrm{height}\right),{\mathrm{R}}^2=0.896;\mathrm{SEE}=0.542. $$

#### Body composition, height and cardiometabolic risk factors

Body height will be measured with the head positioned in the Frankfurt plane with a wall-mounted stadiometer and body composition with a bioelectrical impedance device (InBody 720, Seoul, South Korea; [113]). Venous blood samples will be drawn after standard overnight (12 h) fast. Serum insulin will be measured by electrochemiluminescence immunoassay (Immulite 2000, Siemens, Germany). Fasting plasma glucose, total plasma cholesterol, plasma high and low-density cholesterol and plasma triglycerides will be measured by enzymatic colorimetric assays (Konelab 20XTi, Thermo, USA). Insulin sensitivity estimated by the Homeostatic Model Assessment for Insulin Resistance (HOMA-IR) will be calculated using the formula: fasting serum insulin x fasting plasma glucose/22.5 [114]. White and red blood cells, hematocrit and hemoglobin will be measured by an automated analyzer (Sysmex XP300, Sysmex, Japan). Systolic and diastolic blood pressure, aortic pulse wave velocity, and augmentation index will be measured in supine position with a non-invasive oscillometric device after 10 min of rest (Arteriograph, Tensiomed Ltd., Budapest, Hungary; [115]). Participants will be allowed to drink water and take their usual medications during fastening.

